**Fig. 5 Fig5:**
[figure not shown]
ATM conceptual framework

Of the seven *talukas* which qualified for the intervention, we randomly chose three *talukas* using the online random number generating tool (Available at http://www.random.org/; see Additional file 2). The three *talukas* chosen were Koratagere, Sira and Turuvekere. Some characteristics of the three *talukas* are presented in Table 2. PHCs across the three *talukas* were randomly assigned to one of three arms (A, B and C) of the study intervention. In Arm A, PHCs will receive a package of interventions to optimise service delivery, while Arm B, they will receive Arm A package as well as an additional package of interventions to strengthen existing community participation platforms for organising NCD care at PHC. PHCs in Arm C will be the control. The package of activities in A, B and C are described in Table 3. A detailed description of the intervention and the underlying assumptions behind the activities proposed is provided in Additional file 3 and step-wise plan of rolling out of the intervention is presented in Fig. 6.

**Table 2 Tab2:** Characteristics of study talukas

Characteristics	Koratagere	Sira	Turuvekere
Area	652 Sq km	1552 Sq km	778 Sq km
Population	160,952	301,473	174,297
Number of private pharmacies	19	30	22
General adult literacy rate	71 %	67 %	73 %
Number of PHCs	11	17	11
Average population per PHC	14,500	18,000	16,000
Number of private hospitals/clinics	21	64	18
Number of PHCs with qualified MBBS doctors (of) total number of PHCs in *taluka* (as on March 2014)	11 of 11	15 of 17	10 of 11

(Source: Census 2011)

**Table 3 Tab3:** Description of activities planned under the study intervention arms

Intervention arm	Intervention name	Intervention input	Activities
A	Optimise service delivery	Orientation training & workshop for PHC medical officers	Training on standard treatment guidelines for NCDs, rational prescription, maintaining treatment cards for patients with NCDs and conduction of health days for NCD care.
		Training workshop for pharmacists	Training on need assessment for medicines, counselling patients on medicines and their side effects and non- drug treatment, indenting for medicines and record keeping at PHCs.

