		Training workshop for ANMs, ASHAs and Anganwadi workers.	Orientation on lifestyle modification for NCD, need for long-term follow-up and medication for NCD, availability of free generic medicines for NCD at local PHCs and ensuring that patients visit the PHC regularly for follow-up and medicines.
		Advocacy and coordination.	Coordination and advocacy at state, district and taluka levels with different stakeholders to ensure supply of drugs to the PHCs through routine supply chain, district PIP or utilising local funds (ARS).
B	(Optimise service delivery) + Strengthen existing community participation through patient groups and ARS	Development and dissemination of awareness material.	Awareness material shall focus on lifestyle modification for NCD, need for long-term follow-up and medication for NCD, and availability of free generic medicines for NCD at local PHCs. Disseminate material among health workers, local community groups (ARS, VHSC).
		Formation of NCD patient groups.	To organise NCD patients group meeting and inform about the importance of regular treatment and the advantages of generic medicines
		BCC at community level.	Health worker spreading information leaflets about diabetes & hypertension, about the designated NCD check up day event held 1–3 times per year at the PHC. Information on NCD control will also be displayed at prominent places in the PHC and local villages
		Meeting with ARS members.	Orientation of ARS members about their functions and possibility of utilizing untied funds for purchasing medicines for NCD and facilitate their interaction with patient groups and PHC staff
C (Control)	No intervention	Government existing programme for NCD control at primary health centres.	Government’s making effort at improving generic drug availability. Private pharmacies cater to many NCD patients.

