#### Process documentation

Process documentation forms an integral part of the qualitative component of this study. Quarterly field visits will be conducted to the PHCs and data on utilisation of various services and medicines dispensed for NCDs will be recorded. The patient experiences, PHC staff attitudes towards NCD patients and details of supervisory visits from taluka health officials would be captured. The latter is in order to understand and interpret possibly taluka-wise differences in local leadership and management that could explain differences in performance between PHCs that have received similar inputs.

The interaction with the providers would focus on the motivating factors in case of early adopters and the perceived difficulty in case of others. After each such visit, a detailed narrative report would be prepared. This report would capture unstructured details about: new changes or updates regarding NCD patients in the PHC, responses of PHC staff to the intervention-related developments such as PHC meetings, sub-centre meetings and PHC health days (in the intervention PHCs). In the control PHCs, the field visits will be used to collect new information on any initiatives to detect or treat NCD patients and perspectives on the staff on NCD care.

As part of the community level intervention, we will participate in the patient group meetings and observe whether the group dynamics and the interaction of the group with the PHC have changed/improved, this will be noted and these groups will be purposively approached during the post-intervention data collection.

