#### Difference in difference analysis

Difference in difference estimation will be used to test the effect of the intervention on the outputs. This analysis will adjust for the possibility of other factors like time, institutional factors leading to the output.

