#### Outcome estimation

Outcomes (see Table 9) will be reported as effects of said interventions and represented as risk ratios and odds ratios with 95 % confidence interval.

**Table 9 Tab9:** Measures (indicators) for primary and secondary outcome of interest

Factors to be measured	Indicator
Primary outcome of interest	
Improved and continuous availability of generic drugs at PHC	Percentage of PHC where all generic medicines for NCD patients adequately available in last three months
Increased and regular access to quality medicines for patients with NCD	Percentage of NCD patients/patient groups visit intervention PHC in last three months
Out-of-pocket expenses among patients with NCD	Percentage reduction in median OOP expenditure on medicines per year among NCD patients.
The marginal cost of the intervention to that of the outcome	Incremental cost effective ratio
Improved compliance to standard treatment guidelines by the PHC	Percentage MOs followed prescription practices as per the standard treatment guidelines.
Improved demand of generic drugs among the patients	Percentage increase in patients availing generic drugs from the PHC compared to what it was at three months back
Improved utilization of medicines among NCD patients	Percentage of NCD patients/ patient groups obtained complete and regular medication for last three months.
Secondary outcome of interest	
Better coordination among health staffs with regards to NCD patient group formation	- Percentage increase in number of patient groups formed. - Percentage increase in number of new diabetes patients registered in last three months for a given PHC. - Percentage increase in number of new hypertension patients registered in last three months for a given PHC.
Better drug procurement	Percentage PHCs where drug procurement is up to date for the last quarter.
Conduction of NCD clinics	Percentage PHCs conduct NCD days in last three months
Better reporting and recording by the pharmacists at PHC	Percentage PHCs where medicines were dispensed as prescribed

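### As worded, the primary access indicator in Table 9 counts visits to an intervention PHC, so it has no like-for-like value in the control arm

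*Protocol article*

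**What the plan says.** In the protocol article, Table 9 (Outcome estimation) lists seven primary indicators. The one for access to quality medicines reads "Percentage of NCD patients/patient groups visit intervention PHC in last three months". It is the only row of the table that attaches the word intervention to the PHC; the other rows refer to PHCs in general.

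On the arms, the section on choosing talukas states that "PHCs in Arm C will be the control", and Table 3 gives this arm no intervention. The Process documentation section uses the two terms as opposites. It mentions "PHC health days (in the intervention PHCs") and continues in the next sentence with "In the control PHCs, the field visits will be used to collect new information".

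On analysis, "Difference in difference estimation will be used to test the effect of the intervention on the outputs", and that section says the method is meant to adjust for other factors, time among them. Table 9 outcomes are to be "represented as risk ratios and odds ratios with 95 % confidence interval".

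The indicator also has a double unit, patients or patient groups. The same double unit appears in the primary utilisation indicator, "Percentage of NCD patients/ patient groups obtained complete and regular medication for last three months". In Table 3, "Formation of NCD patient groups" is an Arm B input only.

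**The concern.** Both a ratio against control and a difference-in-difference need the same quantity measured in Arm C as in Arms A and B. If the row is applied as it reads, Arm C patients who attend their own PHC are left out of the numerator. Those who travel to an Arm A or B PHC are counted. The arms were allocated among PHCs within the same three talukas, and the Intention-to-treat section already expects contamination, so some crossover is plausible. The control figure would then record contamination under the name of access.

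This is the row that measures increased and regular access to medicines, the central theme of the study. What is at stake is whether that outcome is compared with control at all, or only followed over time in the intervention arms.

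**Working it through.** **Inputs from the article.** The indicator, the Arm C definition, the estimator and the effect measures are as quoted above. The household survey covered all 39 PHCs. The target was 39 × 30 = 1170 households, which matches the stated figure, and the number surveyed was 326 + 482 + 261 = 1069, which matches Table 4. The article gives no figure for PHC use or crossover.

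**Assumptions, for illustration only.**
- p, the share of NCD patients using their own PHC at baseline: 20%, 30% or 40%, the same in every arm.
- s, a time trend common to all arms: 0, 5 or 10 points, so use at endline lies between 20% and 50%.
- c, the share of Arm C patients visiting an Arm A or B PHC: 0%, 2% or 5%, the same at both surveys.
- The intervention has no effect.

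**Difference-in-difference (DiD).** Let I be the proportion in an intervention arm and C that in control, with 0 for baseline and 1 for endline. DiD = (I1 − I0) − (C1 − C0).
- As worded: ((p + s) − p) − (c − c) = s. The result is 0 with no trend, 5 points with a 5-point trend and 10 points with a 10-point trend. The control arm removes nothing.
- Counting visits to the patient's own PHC: ((p + s) − p) − ((p + s) − p) = 0 in every case, which is correct under no effect.
- If crossover grew from 2% to 5% with no trend, the indicator as worded would give (30 − 30) − (5 − 2) = −3 points. Extra care-seeking by control patients would lower the estimate.

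**Ratios at endline.** RR = I1 / C1 and OR = [I1 / (1 − I1)] / [C1 / (1 − C1)], with I1 = p + s and C1 = c. The correct value of each is 1.

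| Use in A or B at endline | Crossover in C | RR | OR |
|---|---|---|---|
| any | 0% | not estimable | not estimable |
| 20% | 5% | 0.20/0.05 = 4 | 4.75 |
| 30% | 5% | 0.30/0.05 = 6 | 8.14 |
| 30% | 2% | 0.30/0.02 = 15 | 21 |
| 50% | 2% | 0.50/0.02 = 25 | 49 |

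Over the whole range with 2–5% crossover, the RR runs from 4 to 25 and the OR from 4.75 to 49. With own-PHC visits counted in all arms, RR = OR = 1 throughout.

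**The case against.** The strongest reply is that the article often uses the word intervention for the whole three-arm study. The Abstract and the Study design section speak of three arms of the intervention, the section on choosing talukas does much the same for A, B and C, Table 3 lists the control under an intervention-arm column, and Covariate-adjusted analyses refers to three intervention groups. On that usage, an intervention PHC could mean any study PHC. This stands as a possible reading. It does not settle the matter, because Process documentation uses the term in the opposite sense and only this row of Table 9 carries the qualifier. Even on the looser reading, an Arm C patient attending an Arm A or B PHC would count as a success for control.

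The reply is right to resist four stronger inferences:
- *That the trial cannot compare access with control at all.* The Abstract names the utilisation outcome without tying it to an arm, the household tool asks about use of PHC services for NCD, households of all 39 PHCs were surveyed, and the same households are to be revisited. The fault is in the wording of one indicator, not in the data.
- *That a useless intervention would show a 30-point effect if own-PHC use were 30% in every arm.* That is an endline-only contrast. Under the planned DiD with no trend, (30 − 30) − (0 − 0) = 0.
- *That the before-after comparison fails because no PHC was yet an intervention PHC at baseline.* Baseline visits can be counted by the arm to which each PHC was allocated. That change is computable; what is lost is its control.
- *That patient groups give Arm B a different denominator.* The household and exit surveys described interview patients or household members, and none samples groups. The double unit is loose wording, with no shown bias.

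**Conclusion.** The point holds for the indicator as worded. If intervention PHC means what it means in Process documentation, the Arm C proportion is zero or consists of contamination. The ratios are then undefined or far from 1 under no effect, and the DiD passes any common time trend through as an effect, point for point while crossover is stable. If the term means any study PHC, the numerator of a primary endpoint is open to two incompatible readings and still needs correcting.

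The lack of a like-for-like control value follows from the text alone. The sizes (a trend of 5 or 10 points; RR 4 to 25 and OR 4.75 to 49 with 2–5% crossover) rest on the assumed rates and show direction and scale only. The documents do not support saying that the study's data or design rule out a valid comparison.

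**What to change.** Reword the Table 9 row as: *percentage of surveyed NCD patients who visited the PHC serving their village for NCD care in the last three months*. Take it from the household survey, with the same definition in Arms A, B and C at baseline and endline. Report visits by Arm C households to Arm A or B PHCs as a separate contamination measure, which the planned contamination-adjusted analysis can use.

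As a minor tidy-up, drop patient groups as a unit from this row and from the primary utilisation row, since forming such groups belongs to Arm B only.

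The cost is a change of wording. Villages were listed under each PHC before sampling, so the PHC serving each household is known, and PHC use for NCD is already asked. One check is needed: the questionnaire is in an additional file that is not shown here, so confirm that the baseline item identifies the PHC visited and covers the three-month window.

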**Methods:**

This study aims to understand if (and how) a package of interventions targeting primary health centres and community participation platforms affect utilisation and access to generic medicines for people with non-communicable diseases in the current district context in India. This study will employ a quasi-experimental design and a qualitative theory-driven approach. PHCs will be randomly assigned to one of three arms of the intervention. In one arm, PHCs will receive inputs to optimise service delivery for non-communicable diseases, while the second arm will receive an additional package of interventions to strengthen community participation platforms for improving non-communicable disease care. The third arm will be the control. We will conduct household and facility surveys, before and after the intervention and will estimate the effect of the intervention by difference-in-difference analysis. Sample size for measuring effects was calculated based on obtaining at least 30 households for each primary health centre spread across three distance-based clusters. Primary outcomes include availability and utilisation of medicines at primary health centres and out-of-pocket expenditure for medicines by non-communicable disease households. Focus group discussions with patients and in-depth interviews with health workers will also be conducted. Qualitative and process documentation data will be used to explain how the intervention could have worked.

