### Study design and conceptual framework

In this study, we use a quasi-experimental approach along with a theory-driven evaluation to study an intervention for improving access to medicines for diabetes and hypertension at PHCs in Tumkur district of Karnataka, India. We will use a quantitative before-after quasi-experimental study design to understand determinants of improved access to medicines, and a qualitative theory-driven evaluation approach to answer the *how* questions. All PHCs (39 PHCs) across three selected *talukas* were randomly assigned to one of three arms of the intervention. A baseline and an endline survey of households, PHCs and private pharmacies will be conducted for the before-after quasi-experimental component.

The qualitative component of the study will use a theory-driven approach to understand and explain the changes if any, and why the intervention worked for some (where it did) and not for others (where it did not) across the three arms of the study. The theory-driven approach uses successive waves of qualitative data to refine the programme theory, thus resulting in a contextual explanation for how the programme worked in the given setting [25]. In so doing, we shall generate an explanatory theory about improving access to medicines in local health systems in India especially focusing on what works, for whom, and under what conditions, and why. The study design and initial programme theory have been represented in Fig. 2 and Fig. 3. An initial programme theory is an explanation of why the programme is expected to work; it takes into consideration the inputs of the intervention and the assumptions of the implementers on how the intervention inputs could result in the expected outcomes, integrating contextual information from the implementation setting.

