##### End-line survey

After 18 months of the intervention, the survey will be conducted in the same three talukas. The same households (panel survey) that participated in the baseline survey will be visited again with the survey questionnaire.

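### A primary outcome in Table 9, demand for generics, is measured against the level three months earlier; at the 18-month endline that reference is month 15, not the pre-intervention baseline

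*Protocol article*

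**What the plan says.** Under Outcome estimation, Table 9 of the Protocol article lists seven indicators under the primary heading. One is "Improved demand of generic drugs among the patients", and its indicator is "Percentage increase in patients availing generic drugs from the PHC compared to what it was at three months back". The three-month interval is the comparator here. Other primary indicators in the table, on drug availability, PHC visits and complete medication, use the last three months as a window over which a level is observed.

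The timing and the intended contrast are given elsewhere:

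- Study design and conceptual framework: "A baseline and an endline survey of households, PHCs and private pharmacies will be conducted for the before-after quasi-experimental component".
- End-line survey: "After 18 months of the intervention, the survey will be conducted in the same three talukas".
- Abstract, Methods: the study "will estimate the effect of the intervention by difference-in-difference analysis".
- Difference in difference analysis: "Difference in difference estimation will be used to test the effect of the intervention on the outputs".
- Outcome estimation: the outcomes in Table 9 are to be "represented as risk ratios and odds ratios with 95 % confidence interval".

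The section on process documentation also plans quarterly field visits to PHCs that record service use and NCD medicines dispensed. It places these in the qualitative component.

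**The concern.** The design has two survey waves and gets its effect from the change between them, compared across arms. This indicator carries its own reference time, and at endline that time falls inside the intervention period. Whatever was gained by month 15 is in both terms and cancels.

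The indicator then reads recent slope. An arm that gained early and held its gain scores close to zero, while an arm that started late scores high. A control arm that is still drifting upwards can score above an intervention arm that has already levelled off. Because this is a listed primary outcome, following the rule as written could report no effect, or the wrong ordering of arms, where demand had in fact risen.

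Month 15 is also not a survey wave. The comparator would have to come from recall or from another source, and the article names neither for this purpose.

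**Working it through.** The article gives no expected value, effect size or power for this outcome, so there is no stated figure to reproduce. The check is arithmetic on the reference time.

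**Inputs from the Protocol article.** Endline at month T = 18 (End-line survey). Look-back of 3 months (Table 9). Effect estimated as before against after, by difference-in-difference (abstract; Difference in difference analysis).

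**Step 1: reference month.** 18 − 3 = 15. By then arms A and B have had 15/18 = 83% of the intervention period.

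**Step 2: share of the gain kept.** Let f(t) be the uptake curve. In percentage points,

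share kept = [f(18) − f(15)] / [f(18) − f(0)].

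The article gives no f, so the curves below are assumptions chosen to span the possibilities.

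| Assumed uptake | Share kept |
|---|---|
| Immediate step, or plateau by month 6 or 12 | 0% |
| Exponential, half-life 3 months | 2% |
| Exponential, half-life 6 months | 6% |
| Linear over 18 months: 3/18 | 16.7% |
| 6-month lag, then linear: 3/12 | 25% |
| Quadratic: 1 − (15/18)² | 31% |
| 12-month lag, then linear: 3/6 | 50% |
| All uptake after month 15 | 100% |

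Among the lag-then-linear curves, half or more of the gain is kept only when uptake begins at month 12 or later. With the pre-intervention baseline as reference, the share is 100% for every curve.

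**Step 3: the contrast between arms.** Assume the intervention arm goes from 20% to 40% and control from 20% to 25%, with control linear.

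- Baseline to endline: (40 − 20) − (25 − 20) = 15.0 points.
- Month 15 to 18, intervention linear: 20 × 3/18 − 5 × 3/18 = 3.3 − 0.8 = 2.5 points.
- Month 15 to 18, intervention at plateau by month 12: 0 − 0.8 = −0.8 points, so the sign reverses.

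**Step 4: does difference-in-difference rescue the indicator?** Applied to the indicator as worded, it takes growth over months 15 to 18, subtracts growth over the three months before baseline, and compares arms. If pre-baseline growth is the same in all arms it drops out. What remains is the month-15-to-18 contrast of Step 3, not the 15.0 points.

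**Note on scale.** The indicator is a percentage increase, so moving the reference also changes the denominator. With 20% rising linearly to 40%, it reads 40/36.7 − 1 = 9.1%, against 40/20 − 1 = 100% from baseline. Part of that gap comes from the larger base (36.7% instead of 20%). The shares in Step 2 are in percentage points so that this is not counted as lost effect.

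**The case against.** The strongest reply is that Table 9 does not say when the indicator is computed. The quarterly PHC visits run on a three-month cycle and cover control PHCs. Successive quarterly changes, started before the intervention and added up, would recover the whole change. This stands in part: the article does not state that the indicator is computed once, at month 18. But nothing links those visits to this outcome or says that quarters are cumulated, and they are described as process documentation. For the endline survey, the reference time follows from the wording.

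A second reply is that the main effectiveness question survives. That is fair. This is one of seven primary indicators, and the abstract summarises the primary outcomes as availability and utilisation of medicines and out-of-pocket expenditure, without naming demand. The indicators on PHC visits and complete medication are levels, so baseline and endline can be compared without this defect.

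A third reply is that an article may leave such detail to the full protocol. That would cover a missing reference time. Here the reference time is stated, and it conflicts with the design.

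A reader might also infer that the same fault affects the secondary indicator "Percentage increase in number of patient groups formed". It carries no three-month comparator. Whether its base is zero is not stated; Table 3 shows only that forming groups is an Arm B activity. That is a separate question and forms no part of this point.

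**Conclusion.** The point holds. As worded, a listed primary outcome takes its reference from within the intervention period when applied at the 18-month endline, and it does not measure the change since baseline that the design is built to estimate. No section of the article reconciles the two.

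The size is conditional. Across the assumed curves the indicator keeps anywhere from 0% to 100% of the gain, with 16.7% under linear uptake. A reader might infer that most of the effect is necessarily lost. The article does not support that without qualification, because it gives no uptake curve and late uptake would preserve half or more. Nor does it support concluding that the study's other primary comparisons fail, or that difference-in-difference is the wrong analysis. The fault lies in how this one indicator is defined.

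**What to change.** Reword the Table 9 indicator as a level: the percentage of NCD patients who obtained generic NCD medicines from their PHC in the last three months, or the closest item in the baseline survey. Measure it at baseline and endline, and compare the change between arms with the difference-in-difference analysis already planned. Use the quarterly visit data only to describe the trend between surveys.

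The cost is one line of Table 9 and no extra survey wave. There is one constraint: the baseline survey is complete, so the new wording must match something it recorded. The section on the household survey tool lists use of PHC services for NCD, use of medicines and awareness of generic availability at the PHC, but the questionnaire itself is not shown. The investigators should check it before fixing the definition.

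### One of three indicators of the staff-coordination secondary outcome counts an activity assigned to Arm B, so in B vs C and B vs A it measures delivery and not effect

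*Protocol article*

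**What the plan says.** Table 9 (Outcome estimation) has a secondary outcome worded "Better coordination among health staffs with regards to NCD patient group formation". It carries three indicators:

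- the one at issue here, "Percentage increase in number of patient groups formed";
- the rise, PHC by PHC, in people newly registered with diabetes over a three-month window;
- the same measure for hypertension.

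The sentence that introduces the table fixes how all of its rows are used: "Outcomes (see Table 9) will be reported as effects of said interventions", expressed as risk ratios and odds ratios with 95% confidence intervals.

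Table 3 (in the section on the rapid assessment and choice of talukas) lists "Formation of NCD patient groups" in the column of intervention inputs, under Arm B and no other arm. The matching activity begins "To organise NCD patients group meeting and inform about the importance of regular treatment". Arm A receives staff training, advocacy and coordination; Arm C receives no intervention. The first objective treats the forming of patient groups as the route by which drug availability might improve. Under Process documentation the study team adds: "As part of the community level intervention, we will participate in the patient group meetings".

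**The concern.** The same activity appears twice, first as something Arm B is assigned to do and then as evidence of what the assignment achieved. A between-arm difference in the number of groups is expected as soon as the Arm B package is carried out. It says that the community component was implemented. It does not separate better coordination among staff from effort put in by the project.

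If the plan is followed as written, a report could present delivery of the package as an effect on how health staff work together. The comparisons at risk are the two that involve the community package, B vs C and B vs A. The choice of a percentage increase adds a technical problem, because it needs a non-zero starting count and the document gives none.

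**Working it through.** The plan attaches no sample size, power or threshold to this indicator, so there is no figure of its own to reproduce. The check sets the input list against the indicator list, then adds two illustrations.

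**1. Inputs against indicators**

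| Indicator in the Table 9 row | Listed as an input in Table 3? | Arm |
|---|---|---|
| Patient groups formed | Yes | B only |
| New diabetes registrations per PHC | No | – |
| New hypertension registrations per PHC | No | – |

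One of the three indicators duplicates an input.

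**2. Which contrasts are touched**

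- B vs C: the activity is assigned to B and not to C, so the contrast is affected.
- B vs A: the activity is assigned to B and not to A, so the contrast is affected.
- A vs C: the activity is assigned to neither, so the contrast is not affected in this way.

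**3. Illustration: how little delivery would produce a nominal difference**

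This is not a test that the plan prescribes. It turns the count into whether a PHC has at least one group. Assumptions: 39 PHCs split equally, 39 / 3 = 13 per arm (per-arm numbers are not stated), and no groups in control. With k of 13 in Arm B and 0 of 13 in control, the two-sided Fisher p is 2 × C(13,k) / C(26,k).

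| k of 13 in Arm B | Share | Calculation | p |
|---|---|---|---|
| 4 | 31% | 2 × 715 / 14,950 | 0.096 |
| 5 | 38% | 2 × 1,287 / 65,780 | 0.039 |
| 8 | 62% | 2 × 1,287 / 1,562,275 | 0.0016 |
| 13 | 100% | 2 × 1 / 10,400,600 | 1.9 × 10⁻⁷ |

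Under these assumptions, delivery in about 40% of Arm B PHCs gives a nominally significant difference. Nothing about staff coordination enters the calculation.

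**4. Illustration: the percentage increase**

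Suppose 13 groups are added, one per Arm B PHC, to a baseline of b groups. The increase is 100 × 13 / b.

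- b = 5: 260%
- b = 2: 650%
- b = 1: 1300%
- b = 0: undefined

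The same delivery gives very different percentages according to a baseline count that the document does not report. A control arm with no groups would also put a zero in the denominator of the planned risk ratio.

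**The case against.** Several points on the other side stand.

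- **The outcome is worded narrowly.** It concerns coordination in relation to group formation, so counting groups is on topic. This makes the count relevant, but a count in the arm instructed to form groups still shows uptake first.
- **The actor is not named.** Table 3 does not say whether the study team or PHC staff form the groups, and the detailed description is in Additional file 3, which is not shown. If staff form them, the count carries some information on their response. It still would not separate coordination from project effort.
- **Delivery can fail.** The research questions ask how existing arrangements can be strengthened to produce patient groups, and process documentation will record early adopters and difficulties. A low count is possible. That is the behaviour of a fidelity measure.
- **The illustration is not the plan's rule.** The binary outcome, the equal arms and the empty control arm are assumptions. The p values show sensitivity and do not predict a result.

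Two stronger readings are tempting. A reader might infer that the whole secondary outcome is positive by construction. The document does not support this: two of the three indicators are not intervention inputs and can be observed in every arm, and the third depends on delivery succeeding. A reader might also infer that Arms A and C could never show any groups. Nothing rules them out there: patient welfare committees exist under the national mission independently of the study, the Intention-to-treat section anticipates contamination, and visits to control PHCs are planned to record new NCD initiatives.

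**Conclusion.** The overlap between Table 3 and Table 9 is on the page and needs no outside document to see. The group count is an implementation measure in B vs C and B vs A and should not by itself be reported as an effect on staff coordination.

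The reach is limited to one of three indicators, in one secondary outcome, in two of three pairwise contrasts. No sample size and no primary outcome depends on it. The conclusion about delivery rests only on the two tables and the sentence introducing Table 9. The undefined percentage holds only if the baseline count is zero, which is an assumption. The p values hold only under the stated assumptions about arm size and control. The change is worth making because the misreading is easy and the correction is small.

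**What to change.** 1. Take the patient-group indicator out of the Table 9 outcomes that are reported as intervention effects.
2. Report it instead as an implementation count, groups formed per PHC, in all three arms: as delivery in Arm B, and as a contamination check in Arms A and C, where it also serves the contamination-adjusted analysis that the protocol intends to attempt. A count avoids the undefined percentage if the baseline is zero.
3. Base between-arm statements for this row on the diabetes and hypertension registration indicators already listed, and state that they are only indirect measures of coordination.

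No new data are needed, since the count is already to be collected. The cost is one fewer effect indicator for a secondary outcome. The two that remain do not measure coordination directly, so conclusions for this row should be worded with restraint.
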